### MRI acquisition

Brain MRI screening will include T1- and T2-weighted, T2-FLAIR, and time-of-flight angiography sequences. During the study procedure, T1-weighted 3D images are acquired for calculating brain volume (magnetization prepared rapid gradient echo imaging with repetition time/echo time/flip angle of 10.3 ms/4.9 ms/8°). Brain volumes are automatically segmented using FreeSurfer (Athinoula A. Martinos Center for Biomedical Imaging, Massachusetts General Hospital, Boston, MA, USA). All scans performed during the study procedure will be performed on a Philips Ingenia 3T system (Philips Healthcare, Best, The Netherlands) with a 20-channel head–neck coil. A first PCMRI plane is placed at the C2–C3 level of the neck, with the following parameters: retrospective gating using peripheral pulse recording, heart phases = 32, acquired voxel size = 1 × 1 mm with 3-mm slice thickness, repetition time/echo time = 9.2 ms/5.5 ms, flip angle = 10°, and velocity encoding = 80 cm/s. A second PCMRI plane is placed perpendicular to the ascending aorta, thus also transecting the descending aorta, with the following parameters: retrospective gating using peripheral pulse recording, heart phases = 32, acquired voxel size = 2.5 × 2.5 mm with 8-mm slice thickness, repetition time/echo time = 4.2 ms/2.6 ms, flip angle = 10°, and velocity encoding = 150 cm/s. Flow measurements will be performed using Segment version 3.2 R9074 (Medviso AB, Lund, Sweden) [24]. For each voxel of the phase image, velocity (cm/s) is calculated and averaged over the region of interest (ROI). Blood flow rate (mL/min) is then obtained by multiplying the average velocity during the cardiac cycle with the cross-sectional ROI area. The images are manually inspected for signs of aliasing or motion artefacts, and any aliasing is corrected using the built-in feature in Segment. For the C2–C3 planes, vessel lumen segmentation is either manually defined and kept constant across the cardiac cycle or performed with the semiautomatic algorithm, which tracks the vessel throughout the cycle. For the aortic planes, segmentation is performed using the semiautomatic algorithm. Cerebral perfusion will be acquired using pseudo-continuous arterial spin labeling (pcASL), with a single-shot gradient-echo EPI readout. The sequence will be acquired with TR/TE = 4139/13 ms, flip angle = 90°, field of view = 240 × 240 × 150 mm³, and an acquisition matrix of 86 × 68, yielding an acquired voxel size of 2.73 × 3.75 × 5.0 mm³ (reconstructed to 1.88 × 1.88 × 5.0 mm³). 30 transverse slices (0 mm gap) will be collected with parallel imaging (SENSE factor 2.3, AP direction). Labeling will be applied below the imaging slab using a pcASL scheme, followed by a post-labeling delay of 2000 ms. Thirty dynamic control/label pairs will be obtained, with a total scan duration of 7 min 2 s. Fat suppression will be performed using SPIR. All images will be co-registered to the high-resolution T1-weighted anatomical scan. Perfusion maps are quantified using the Oxford ASL script in the BASIL toolbox (FSL, Oxford Centre for Integrative Neuroimaging) [25], following consensus recommendations [26]. Here, voxel-wise control–label differences will be converted to perfusion estimates using a model of MR signal evolution based on acquisition parameters and blood and tissue relaxation properties.

### Hemodynamic characteristics

Total CBF is calculated as the sum of blood flow rates (mL/min) in the left and right internal carotid and vertebral arteries. CO is represented by ascending aorta flow rate, stroke volume is derived from CO divided by heart rate. The flows in the external carotid arteries are summed and interpreted as a characterization of peripheral vascular flow. CVR is calculated as (MAP – ICP)/CBF. SVR is calculated as ([MAP – central venous pressure (CVP)]/CO) × 80. CVP is assumed to be 10 mmHg in both groups [27]. ICP is assumed to be 10 mmHg in MAP-ANE [28], whereas in MAP-SAH the recorded mean ICP from the hour preceding the intervention is used. Flow areas are calculated using ROI for all vessels. Arterial compliance will be calculated from PCMRI-derived flow waveforms and simultaneous arterial pressure data as previously described [29]. An overview of measured and derived variables is provided in Table 2.

**Table 2 pone.0338688.t002:** An overview of all measured and derived variables.

Variable	Source/method	Unit

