### Intervention

Blood pressure and vital signs will be monitored with MRI-compatible equipment Philips Expression MR400 (Philips Healthcare, Best, The Netherlands) during scanning and Philips IntelliVue X2 (Philips Healthcare, Best, The Netherlands) in the operating room and ICU. Invasive continuous blood pressure monitoring is achieved via a radial artery catheter with a fluid-filled line and Xtrans® pressure transducer (CODAN TRIPLUS AB, Kungsbacka, Sweden). Electrocardiogram, pulse oximetry, systolic and diastolic pressure, MAP, and end-tidal carbon dioxide (EtCO₂) are continuously recorded using the respective patient monitoring systems, with all data exported to the PDMS. Administered drugs are entered manually into the PDMS. Arterial blood gases will be sampled immediately before and after the intervention and analyzed using ABL90 FLEX PLUS (Radiometer Medical ApS, Brønshøj, Denmark). For MAP-SAH patients, ICP is continuously monitored in the ICU using an intraparenchymal or intraventricular catheter, with values exported to the PDMS.

As a safety measure, blood pressure elevation is carried out prior to transport to the MRI suite in the operating room (MAP-ANE) or ICU (MAP-SAH). During this manipulation, NIRS measurements are obtained with the INVOS™ 5100C (Medtronic, Minneapolis, MN, USA). Baseline MAP is defined by the attending anesthesiologist according to clinical routines, typically 65–70 mmHg. If NE infusion is already required to maintain this level, it is continued at the same dose and documented as the baseline NE dose. For the blood pressure elevation procedure, NE infusion is titrated stepwise every 2 minutes by 0.01–0.04 μg·kg⁻¹·min⁻¹ until a 25% MAP increase or a systolic pressure limit of 160 mmHg in MAP-ANE and 200 mmHg in MAP-SAH is reached. MRI scans will be acquired at both baseline and elevated MAP. NE (Sintetica, Mendrisio, Switzerland) is prepared as a 40 µg/mL solution and administered via a Braun Perfusor Space pump (B. Braun, Melsungen, Germany), with Plasmalyte (Baxter, Deerfield, IL, USA) delivered by Braun Infusomat Space (B. Braun, Melsungen, Germany) as the carrier. The intervention lasts approximately 90 minutes. All participants are monitored by an anesthesiologist, and NE infusion is discontinued at any sign of adverse response.

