**Measured variables**		
MAP, SAP, DAP	Invasive radial artery catheter	mmHg
Heart rate (HR)	ECG, MRI	beats/min
Oxygen saturation (SpO_2_)	Pulse oximetry	%
End-tidal CO₂ (EtCO_2_)	MR400	kPa
Arterial blood gases	ABL90 FLEX PLUS	kPa and mmol/L
Regional cerebral oxygenation (rSO_2_)	NIRS (INVOS™ 5100C)	%
ICA, VA, ECA blood flow	PCMRI (C2–C3 planes)	mL/min
Aortic blood flow/ cardiac output (CO)	PCMRI (ascending aorta plane)	mL/min
Regional perfusion	ASL (pcASL sequences)	mL/100 g/min
Intracranial pressure (ICP)	Intraparenchymal or intraventricular catheter	mmHg

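### The SVR formula uses the factor 80, which requires cardiac output in L/min, but cardiac output is specified in mL/min, so absolute SVR values computed as written are 1,000 times too small (minor; planned tests unaffected)

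*Protocol article*

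**What the plan says.** All references are to the protocol article.

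- **SVR.** Hemodynamic characteristics: "SVR is calculated as ([MAP – central venous pressure (CVP)]/CO) × 80". The SVR row of Table 2 (calculated variables) has the same formula, with the result in dyn·s·cm⁻⁵.
- **Cardiac output.** Hemodynamic characteristics: "CO is represented by ascending aorta flow rate, stroke volume is derived from CO divided by heart rate". Table 2 (measured variables) lists it as "Aortic blood flow/ cardiac output (CO) PCMRI (ascending aorta plane) mL/min". MRI acquisition gives the unit of every phase-contrast flow: "Blood flow rate (mL/min) is then obtained by multiplying the average velocity during the cardiac cycle with the cross-sectional ROI area".
- **Stroke volume.** Table 2 defines it as CO divided by heart rate, in mL/beat.
- **CVP.** "CVP is assumed to be 10 mmHg in both groups".
- **CVR.** "CVR is calculated as (MAP – ICP)/CBF", with total CBF in mL/min. Table 2 prints the unit as mmHg·mL⁻¹·min⁻¹.

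No step converting CO to L/min appears in the text or in Table 2.

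**The concern.** The article defines one quantity, CO, with one unit, and uses it in two formulas. The stroke volume formula works with that unit; the SVR formula does not. The factor 80 is the usual constant for turning mmHg per L/min into dyn·s·cm⁻⁵. An analyst who puts CO into the SVR formula in the unit given in Table 2 gets a number near 1, labelled with a unit in which the value should be several hundred or more.

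What is at stake is descriptive reporting. Statistical methods plans medians with interquartile ranges as the general form of description, and resistance is among the variables whose change is tested. Any absolute SVR level or absolute SVR change reported from the formula as written would be wrong for its stated unit. The planned rank-based tests would not expose this, because they do not depend on scale.

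The CVR unit is a separate and smaller matter. Pressure divided by flow in mL/min carries minutes in the numerator, whereas the printed unit has them in the denominator.

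**Working it through.** **Inputs.** Formula, factor 80 and CVP 10 mmHg: Hemodynamic characteristics. CO in mL/min: Table 2 and MRI acquisition. MAP: Intervention, "Baseline MAP is defined by the attending anesthesiologist according to clinical routines, typically 65–70 mmHg", with a target rise of 25%. The document gives no CO values, so 5,000 mL/min (range 4,000 to 6,000) is an assumption for illustration. Unit definition: 1 mmHg = 1333.22 dyn/cm².

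**Step 1: reproduce the factor 80.** With CO in L/min, 1 L/min = 1000/60 = 16.667 cm³/s, and 1333.22 / 16.667 = 79.99. The factor 80 is correct for L/min.

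**Step 2: the factor for the specified unit.** With CO in mL/min, 1 mL/min = 1/60 cm³/s, and 1333.22 × 60 = 79,993, or about 80,000. The factor 80 does not reproduce. The ratio is 80,000 / 80 = 1,000, whatever CO is.

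**Step 3: confirm that CO is meant in mL/min elsewhere.** Stroke volume = CO / HR. (mL/min) / (beats/min) = mL/beat, which is the printed unit. With CO in L/min the result would be L/beat. So the same CO entry cannot serve both rows without a conversion.

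**Step 4: size.**

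| MAP (mmHg) | Assumed CO (mL/min) | As written: (MAP − 10)/CO × 80 | CO in L/min: (MAP − 10)/(CO/1000) × 80 |
|---|---|---|---|
| 65 | 6,000 | 55/6000 × 80 = 0.73 | 733 |
| 70 | 5,000 | 60/5000 × 80 = 0.96 | 960 |
| 70 | 4,000 | 60/4000 × 80 = 1.20 | 1,200 |

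**Step 5: what a constant factor changes.** Take MAP from 70 to 70 × 1.25 = 87.5, with CO held at the assumed 5,000 mL/min. As written, SVR goes from 0.96 to 77.5/5000 × 80 = 1.24, a change of 0.28. With CO in L/min it goes from 960 to 1,240, a change of 280. The absolute change is off by 1,000. The percentage change is not: 0.28/0.96 = 280/960 = 29.2%. The signed-rank test uses only the signs and ranks of the paired differences, and Spearman's coefficient only ranks; dividing every value by 1,000 leaves both unchanged. A simulated check with 18 pairs gave the same p-values before and after division (Wilcoxon 0.0056 both times, Spearman 0.598 both times).

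**Step 6: CVR.** mmHg / (mL/min) = mmHg·min·mL⁻¹. The printed unit has min⁻¹ where it should have min⁺¹. The formula contains no conversion constant, so the values are right: for example (70 − 10)/600 = 0.10 mmHg per mL/min, with an assumed CBF of 600 mL/min and the ICP of 10 mmHg that the article assumes for MAP-ANE.

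**The case against.** The strongest reply is that the SVR row itself shows what was meant. The factor 80 together with a result in dyn·s·cm⁻⁵ implies CO in L/min, so the defect is probably an unstated conversion and not a wrong calculation. A value near 1 would be conspicuous, and a known constant can be undone at any time by multiplying by 1,000. All of this stands, and it limits the severity. It does not remove the defect, because the article fixes CO in mL/min and nowhere says that it is converted.

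A reader might infer more than the document supports, in four ways:

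- **That the absolute levels of SVR and CVR are secondary outcomes in their own right.** The Outcomes section lists the analysis of associations between systemic and cerebral parameters, with SVR and CVR among the examples. Their absolute levels are not listed there.
- **That the planned inferences on resistance are unsound.** Step 5 shows that the tests, correlations and percentage changes are the same with either constant. That the tests cannot reveal the error also means that the error cannot harm them.
- **That CVR is miscalculated too.** Only its unit label is wrong.
- **That wrong SVR results already exist.** The Study design section says that no results have been generated.

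**Conclusion.** The point holds and is minor. The SVR rule, followed with the unit the article gives for CO, returns absolute values and absolute changes too small by a constant factor of 1,000. That factor follows from unit definitions alone; only the illustrative values depend on the assumed CO. The primary outcome (change in total CBF) and the sample size do not use SVR or CVR. The CVR entry is a labelling slip with no numerical consequence. The conclusion assumes that no fuller document states a conversion of CO to L/min. If one does, the article still needs the correction, because its own entries conflict.

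**What to change.** Three entries change:

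1. In the Hemodynamic characteristics text, state that CO enters the SVR formula in L/min. Alternatively, keep CO in mL/min and replace 80 with 80,000.
2. Make the same change in the SVR row of Table 2. CO can stay in mL/min in its own row, so stroke volume in mL/beat remains correct.
3. In the CVR row of Table 2, print the unit as mmHg·min·mL⁻¹ (mmHg per mL/min), and leave the formula as it is.

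The analysis code should use the same convention. The cost is an editorial correction, with no change to data collection, procedures, tests or sample size. Recruitment is still under way, so it can be made before any SVR value is reported.

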**Measured variables**		
MAP, SAP, DAP	Invasive radial artery catheter	mmHg
Heart rate (HR)	ECG, MRI	beats/min
Oxygen saturation (SpO_2_)	Pulse oximetry	%
End-tidal CO₂ (EtCO_2_)	MR400	kPa
Arterial blood gases	ABL90 FLEX PLUS	kPa and mmol/L
Regional cerebral oxygenation (rSO_2_)	NIRS (INVOS™ 5100C)	%
ICA, VA, ECA blood flow	PCMRI (C2–C3 planes)	mL/min
Aortic blood flow/ cardiac output (CO)	PCMRI (ascending aorta plane)	mL/min
Regional perfusion	ASL (pcASL sequences)	mL/100 g/min
Intracranial pressure (ICP)	Intraparenchymal or intraventricular catheter	mmHg
**Calculated variables**		
Stroke volume	CO ÷ HR	mL/beat
Total CBF	Sum of bilateral ICA + VA flows	mL/min
External carotid artery flow	Summed ECA flows	mL/min
Cerebrovascular resistance (CVR)	(MAP – ICP) ÷ CBF	mmHg· mL^-1^· min^-1^
Systemic vascular resistance (SVR)	([MAP – CVP] ÷ CO) × 80	dyn· secs· cm^-5^
Brain volume	FreeSurfer automated segmentation of T1-weighted sequence	mL
Arterial compliance	Windkessel model, ratio of pulsatile volume to pressure	mL/mmHg

MAP, mean arterial pressure; SAP, systolic arterial pressure; DAP, diastolic arterial pressure; NIRS, near-infrared spectroscopy; ICA, internal carotid artery; VA, vertebral artery; ECA, external carotid artery; CO, cardiac output; PCMRI, phase-contrast magnetic resonance imaging; ASL, arterial spin labeling; CBF, cerebral blood flow; ICP, intracranial pressure; CVP, central venous pressure.

### Sample size

A non-inferiority margin of +15% is specified as the minimal clinically important increase in total CBF. This threshold exceeds expected measurement repeatability and short-term biological variability for PCMRI [30] and remains conservative relative to prior transcranial Doppler data in traumatic brain injury and critically ill patients reporting ~20% increases in cerebral blood flow velocity at ~30% MAP elevation [15]. To minimize type II error, the study is powered at 95% (two-sided α = 0.05). Missing a true increase in global CBF would have direct clinical implications, as it could falsely support withholding potentially beneficial MAP augmentation. Sample size estimation is based on the standard deviation of CBF change observed in prior experimental studies of healthy volunteers. To account for greater expected heterogeneity in anesthesia and ICU patients, this standard deviation was conservatively doubled. Under these assumptions, the required sample size is 18 analyzable paired datasets per cohort. Allowing for ~10% attrition, we plan to enroll 20 participants per study population (MAP-ANE and MAP-SAH).

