### Outcomes

The primary outcome is the change in total CBF between baseline and elevated MAP, thereby directly testing whether induced hypertension increases CBF. Secondary outcomes include additional perfusion measurement with ASL, characterization of the slope of the MAP–CBF relationship, and analysis of associations between systemic and cerebral hemodynamic parameters, such as cardiac output (CO), systemic vascular resistance (SVR), cerebrovascular resistance (CVR), and arterial compliance. Further, changes in rSO_2_ relative to CBF will be analyzed to evaluate its validity as a surrogate marker. Safety parameters, including arrhythmias, bradycardia, or other adverse responses during NE infusion, are monitored continuously. Events severe enough to require interruption of the procedure and discontinuation of NE infusion are documented in the CRF.

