### Statistical methods

All analyses will be performed using SPSS (IBM Corp., Armonk, NY, USA). Given the relatively small sample size, assumptions of normality cannot be reliably validated; therefore, non-parametric tests will be used. Descriptive statistics will be reported as medians with interquartile range unless otherwise specified. Changes in flow, pressure, resistance, arterial compliance, and vessel area between baseline and elevated MAP will be analyzed using the Wilcoxon signed-rank test. Correlations between systemic and cerebral hemodynamic variables will be explored using Spearman’s rank correlation. A two-sided p-value <0.05 will be considered statistically significant.

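### The important increase in CBF is set as a percentage, but the primary outcome and its test are written in mL/min, so no planned result is on the scale of the +15% margin

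*Protocol article*

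**What the plan says.** Four parts of the protocol article bear on this.

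- **Sample size.** "A non-inferiority margin of +15% is specified as the minimal clinically important increase in total CBF". The margin is defended by PCMRI repeatability and by transcranial Doppler data, where velocity rose by about 20% for a MAP rise of about 30%. On the spread, the section says "Sample size estimation is based on the standard deviation of CBF change observed in prior experimental studies of healthy volunteers", and then "this standard deviation was conservatively doubled". It gives neither a value nor a unit for that SD. The result is that "the required sample size is 18 analyzable paired datasets per cohort", with 95% power at two-sided 0.05.
- **Outcomes.** "The primary outcome is the change in total CBF between baseline and elevated MAP". Absolute or relative is not stated.
- **Hemodynamic characteristics and Table 2.** "Total CBF is calculated as the sum of blood flow rates (mL/min) in the left and right internal carotid and vertebral arteries". The calculated variables in Table 2 include no percent change.
- **Statistical methods.** "Changes in flow, pressure, resistance, arterial compliance, and vessel area between baseline and elevated MAP will be analyzed using the Wilcoxon signed-rank test". Significance is a two-sided p below 0.05. No interval, and no comparison with +15%, is mentioned.

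**The concern.** The effect that matters is expressed on one scale and the primary analysis, on its plain reading, on another. No sentence connects them.

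A signed-rank result depends on the scale. Ranks of mL/min differences are not ranks of percent changes, so the p-value and any location estimate can differ. On the mL/min scale, a given percentage change earns a larger rank in a patient with high baseline flow. For illustration, a 15% rise is 0.15 × 400 = 60 mL/min in one patient and 0.15 × 800 = 120 mL/min in another.

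Two things are at stake. The reader of the primary result could not place it against the trial's own threshold without a further, unplanned step. And if the scale stays unstated, it can be chosen after the data are seen. The Sample size section itself warns that missing a true increase could wrongly support withholding MAP augmentation.

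**Working it through.** **1. The plan's own figures.** Enrolment reproduces: 18 / (1 − 0.10) = 20. The 18 cannot be derived forward because the SD is missing. Solving backwards for a 15-point change:

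- Normal formula: SD = 15 × √18 / (1.960 + 1.645) = 17.7 points, so a volunteer SD of about 8.8 before doubling.
- Paired t (noncentral): SD = 16.6 points, volunteer SD about 8.3. An SD of 16.1 would already be met by 17 pairs, so 18 is the smallest sufficient n for SDs between 16.1 and 16.6.

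This back-calculation assumes that the SD was in percentage points. Had it been in mL/min, +15% must first be converted through a mean baseline that the documents do not give: 75, 90, 105 or 120 mL/min for an assumed 500, 600, 700 or 800. The text cannot show which was done.

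**2. Cost of the scale to the written test (null of zero change).** Assumptions: n = 18, true mean rise +15%, SD 16.6 points, response unrelated to baseline, lognormal baseline with mean 600 mL/min and CV 20-40%. The baseline figures are assumed. By simulation:

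| Scale | Power |
|---|---|
| Percent change | about 94% |
| mL/min | about 92.4% to 93.6% |

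The loss is 0 to 2 points.

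**3. Reading the result against the margin.** The protocol plans no such step; this shows what would follow if one were added. The true mean rise is exactly +15%, and the table gives how often a Hodges-Lehmann upper 97.5% bound falls below the margin (90 mL/min on the absolute scale, that is 15% of 600).

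| Correlation of response with baseline | Percent scale | mL/min scale, CV 20 / 30 / 40% |
|---|---|---|
| 0 | 2.1-2.5% | 3.0 / 3.7 / 4.7% |
| −0.25 | 2.1-2.5% | 3.5 / 4.7 / 6.6% |
| −0.5 | 2.1-2.5% | 3.9 / 6.3 / 9.7% |

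At −0.5 the mean mL/min change, as a share of mean baseline, is 15 − 0.5 × 16.6 × s, where s = √ln(1 + CV²). For CV 20%, s = 0.198 and the result is 13.4%. For CV 40%, s = 0.385 and the result is 11.8%. Power of the written test against zero would then be about 86% to 90%.

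**The case against.** The best case against is that the article is silent rather than contradictory. A unit for total CBF does not fix the scale of its change, and a percent change is also a change in flow. A condensed article may leave that to an analysis plan. What weakens this is that the article does state outcome, unit, test and margin, and as stated they do not meet.

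Several stronger readings are tempting, and the documents do not support them:

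- *The margin is relative to each patient's own baseline.* No denominator is given. The paired design makes this the natural reading, but a rise over the group's mean or median baseline also fits.
- *The sample size is for a percentage effect that the test does not analyse.* The planning SD has no unit, so this cannot be established.
- *A mL/min analysis could never be compared with +15%.* It could: elevated flow can be tested against 1.15 × baseline, wholly in mL/min. The protocol simply does not plan this.
- *The mL/min scale biases the trial toward no increase.* This needs low-flow patients to respond more in percentage terms. The Introduction links the response to autoregulatory status, not to baseline flow. The 11.8-13.4% figures describe change in aggregate flow, a different summary rather than an error, and the error rates belong to a bound that is not in the protocol.

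It is also fair to say that the test of zero change never uses the margin at all, which is a weightier and separate matter. Repairing it would still require a choice of scale.

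**Conclusion.** The point holds in limited form. The threshold is a percentage, the primary analysis reads as mL/min, and nothing planned yields a result on the threshold's scale. This is a gap in interpretability and pre-specification, not a demonstrated loss of validity.

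On power alone the effect is 0 to 2 points, given the SD, baseline and independence assumptions in step 2. If a margin comparison were added in mL/min, the error at the margin would be about 3% to 5% instead of about 2.5% with response unrelated to baseline. It would approach 10% only with an assumed correlation of −0.5 and a baseline CV of 40%. A correction is worth making because it is cheap and recruitment is still under way in both cohorts.

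**What to change.** In Outcomes and Statistical methods, define the primary variable as each patient's percent change in total CBF, 100 × (elevated − baseline) / baseline. The log ratio would serve equally well, with the margin at ln(1.15) = 0.140. In Sample size, give the planning SD in that same unit and say what the 15% is a percentage of. Report the signed-rank test on that variable with a Hodges-Lehmann estimate and 95% confidence interval, so that the result can be read against +15%. Keep the mL/min change as a secondary description.

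The cost is a few sentences and one computed variable, with no new data or patients. The downside is small: a ratio to a noisy baseline is somewhat more sensitive to baseline measurement error, which is a reason to show the mL/min result beside it.

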This protocol describes two parallel studies applying identical MRI-based methodology in combination with continuous invasive blood pressure monitoring and NIRS: MAP-ANE in elective anesthesia patients and MAP-SAH in sedated ICU patients with aSAH. The objective is to characterize MAP–CBF relationships under these two conditions, test the hypothesis that blood pressure augmentation does not increase CBF, and explore interactions between the cerebral and systemic circulation. A further aim is to assess the validity of NIRS as a surrogate marker for CBF changes across different blood pressure levels.

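### The +15% margin sizes each cohort but never enters the analysis, so a non-significant Wilcoxon test could be taken as evidence that CBF does not increase

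*Protocol article*

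**What the plan says.** The Introduction of the protocol article gives the aim as to "test the hypothesis that blood pressure augmentation does not increase CBF"; the Discussion repeats it.

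The Sample size section adopts a margin: "A non-inferiority margin of +15% is specified as the minimal clinically important increase in total CBF". It continues: "the study is powered at 95% (two-sided α = 0.05"), and presents the high power as protection against missing a real increase, because such a miss could wrongly justify not raising MAP. The SD comes from healthy-volunteer studies and "this standard deviation was conservatively doubled", but no value is given. The result is that "the required sample size is 18 analyzable paired datasets per cohort", with 20 enrolled.

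The Statistical methods section says that changes in flow and other variables "between baseline and elevated MAP will be analyzed using the Wilcoxon signed-rank test", and that "A two-sided p-value <0.05 will be considered statistically significant". Total CBF, the primary outcome, is a flow, so this is the rule that governs it. The section mentions no margin, no shifted null and no confidence interval.

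**The concern.** The two sections describe different inferences. A margin belongs to a claim that any increase is smaller than a stated amount, which is shown by rejecting the null that the increase is 15% or more. A signed-rank test on the change, in its ordinary form, asks whether the change differs from zero. Failing to reject zero does not show that there is no increase, nor that an increase of 15% has been excluded.

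This matters because the hypothesis is itself one of no increase. A non-significant p-value could be read as confirming it. The Sample size section names the harm of that error, but guards against it only through power, and so only as far as an unstated SD turns out to be right. Under a margin rule the same false claim would be limited by alpha whatever the SD. Both items are stated in the article, so this is a conflict in the plan and not a detail left for a separate analysis plan.

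**Working it through.** **Inputs from the Sample size section:** margin 15%, power 95%, two-sided alpha 0.05, 18 analysable pairs, about 10% attrition. The SD of the change is not given.

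**1. The plan's own figure.** The number 18 cannot be derived forward without the SD, so I solve for the SD.
- Normal approximation: n = [SD × (1.960 + 1.645) / 15]², so SD = 15 × √18 / 3.605 = 17.7 points (17.65).
- Noncentral t: 95% power at n = 18 needs a standardised change of 0.9025, so SD = 15 / 0.9025 = 16.6 points.
- Before doubling, the volunteer SD would be about 8.3 to 8.8 points.
- Attrition reproduces: 18 / 0.90 = 20.

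**2. What a non-significant result can hide.** On a t basis with SD 16.6, the 95% half-width is 2.110 × 16.6 / √18 = 8.3 points. A result that just misses significance has an upper limit of about 2 × 8.3 = 16.5 points (before rounding the half-width), which is above the margin.

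**3. The two rules compared by simulation.** There were 20,000 trials per scenario, n = 18, with normal differences on the percent scale. The written rule is a two-sided Wilcoxon test against 0 at 0.05. The margin rule is a Wilcoxon test against +15% at one-sided 0.025.

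| SD (points) | True change | Non-significant vs 0 | +15% excluded | Non-significant and +15% not excluded |
|---|---|---|---|---|
| 16.6 | 0 | 95.2% | 93.7% | 5.0% |
| 16.6 | +5% | 78.8% | 65.0% | 18.4% |
| 16.6 | +10% | 35.2% | 21.3% | 18.2% |
| 16.6 | +15% | 6.1% | 2.4% | 4.6% |
| 17.65 | 0 | 95.2% | 91.2% | 7.1% |
| 17.65 | +5% | 80.5% | 59.5% | 24.1% |
| 17.65 | +10% | 40.0% | 19.4% | 23.4% |
| 17.65 | +15% | 8.7% | 2.4% | 7.0% |
| 25 (assumed) | 0 | 95.2% | 64.1% | 33.7% |
| 25 (assumed) | +15% | 34.8% | 2.5% | 32.4% |

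The roughly 2.5% in the +15% rows is the nominal level of the margin rule, so it holds by construction. It does not move with the SD, whereas the miss rate of the written rule rises from 6-9% to 35%.

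**4. Does n = 18 serve a margin analysis?** The t-test arithmetic is symmetric: 95% power to detect +15% against 0 is also 95% power to exclude +15% when the truth is 0. The signed-rank version gives 91-94% at the back-solved SD.

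**The case against.** The strongest defence is that two-sided alpha, type II error as the missed increase, 15% as the effect to detect and a two-sided Wilcoxon test together make a coherent difference design. The Outcomes section also frames the primary outcome as asking whether CBF increases. If the implied SD holds, an increase at the protocol's own threshold is missed in only 6-9% of trials. This stands, and it limits the size of the problem. On that reading, however, the term non-inferiority margin is wrong, the two sections still need reconciling, and a non-significant result still does not establish the hypothesis.

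Four stronger readings are tempting, and the article does not support them:
- A reader might infer that the sponsor has committed to reporting p≥0.05 as no increase. No sentence says so. The hypothesis and the worry about a missed increase make it plausible, no more.
- A reader might conclude that the primary conclusion is unsupported whatever the result. It is not: the Introduction reports a fall in CBF in healthy volunteers, and a significant decrease would support the hypothesis under either rule.
- A reader might expect small significant increases that also lie inside the margin to be common. At the back-solved SD, an observed +7% has an interval of about −1.3% to +15.3%, which is neither significant nor inside the margin. For both to hold, the SD must be below 7 × √18 / 2.110, about 14 points. At SD 10 and a true +5%, 47% of trials would show both; at SD 16.6 to 17.65 it is about 3-5%.
- A margin in percent beside flow in mL/min is no defect, since percent change follows from the paired values.

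A true +10% also lies below the protocol's threshold, so a finding of no important increase would then be correct. What counts there is the 18-24% of trials that are non-significant yet have not excluded +15%.

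**Conclusion.** The conflict is real and concerns the primary outcome of both studies. The plan names a margin for a no-increase hypothesis and then analyses the outcome without it. Only a non-significant result is exposed. At the back-solved SD of 16.6 to 17.7 points, the written test is non-significant in about 6-9% of trials at a true +15%, against 2.5% under a margin rule. At a true +5% or +10%, about 18-24% of trials are non-significant while leaving +15% open.

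The figures assume normal differences on the percent scale and an SD inferred from n = 18. The 25-point SD is my assumption and lies above a value that the sponsor says was already doubled; there, a true +15% is missed in about 35%. That the signed-rank null is zero change is the default form of the test and is not written out in the article.

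This should be settled before any data are analysed. The Study design section says that no results exist yet, so the rule can still be set without knowledge of the data.

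**What to change.** For the primary outcome, analyse the per-patient percent change in total CBF, for example as the log ratio of elevated to baseline flow (margin ln 1.15 = 0.140). Report the Hodges-Lehmann estimate with the 95% confidence interval from the signed-rank test, back-transformed to percent. State the decision rule:
- *no clinically important increase* only if the upper limit is below +15%;
- *increase* if the lower limit is above 0;
- both statements if both hold;
- otherwise *inconclusive*.

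Restate the Sample size section so that a false claim of no important increase is controlled at one-sided 2.5%. Give the SD used, and from it the power to exclude +15% at a true change of 0 with 18 pairs, on the scale chosen for analysis. At the back-solved SD this is about 91-94%, not 95%; at an SD of 25 points it would be about 64%. If 15% was meant only as a detectable difference, drop the non-inferiority label and say that a non-significant result will not be reported as showing no increase.

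The cost is wording, a slightly lower stated power and some results labelled inconclusive. The analysis stays non-parametric and no new patients are needed.
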